### Study population

#### Organisations

Organisations that fit the criteria of being an SME will be invited to participate in the study. SMEs are defined as organisations with fewer than 250 employees [9]. A small sized enterprise is defined as an organisation with fewer than 50 employees and a medium-sized enterprise consists of 50–249 employees. Definitions and inclusion criteria of the SMEs in the construction, healthcare and ICT sectors are based on Nomenclature of Economic Activities (NACE) guidelines [59]. The aim is to recruit a minimum of two SMEs from each of the three targeted sectors, construction, healthcare and ICT, across the nine participating countries: Australia, Albania, Ireland, Netherlands, Hungary, Kosovo, Germany, Finland and Spain. If significant issues arise with the recruitment of SMEs as per the strict criteria, consideration will be given to broaden the definition to include slightly larger organisations (e.g. 300 employees).

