### Sample size

In each of the nine countries, local research officers will use convenience sampling to recruit a minimum of two SMEs in each of the three sectors, yielding a total of at least 54 participating SMEs, half for intervention and half for control. An average of 65 participants per SME will be recruited at baseline. Allowing for an estimated attrition rate of 65%, based on the pilot study and previous literature [60, 61], this will yield baseline and follow-up data for 23 participants per SME. A sample size of 621 participants (i.e. 27 SMEs with 23 participants) in each arm of the cRCT achieves 85% power to detect a difference of 0.25 standard deviations between the mean change in intervention participants and the mean change in control participants, when the intra-cluster correlation is 0.05, using a two-sided independent *t*-test with a significance level of 0.05.

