### Randomisation of SMEs

Local research officers will assign a pseudonym to each participating SME. SMEs will be allocated to either the intervention or control conditions using block randomisation. This will be completed by the evaluation team, who remain blinded to the identity of the SMEs. To maintain balance between the intervention and control groups, group allocation will be conducted in pairs of SMEs within each sector in each country. This process will be repeated to create a list of SMEs with group allocation. Minimisation is expected to be used when an unpaired SME is required to be allocated to a condition [65]. The first SME will be allocated to the intervention or control group at random. The allocation status of the subsequent SME will be determined based on the allocation of the first SME in a manner that would lead to better balance between the groups in the variables of interest.

After randomisation is complete, the local research officers will contact each SME to inform them of their randomisation status. The meeting will involve discussing the appointment of the designated communications person within the SME, the purpose of the surveys and what is involved in them and clarifying the details of implementing and scheduling the introductory sessions within the SME. Participants and the local research officer will not be blinded to allocation status; however, analysts evaluating the outcome will be blinded.

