### Economic evaluation

A cost-consequence analysis will be conducted to compare differences in costs and outcomes between the intervention and control groups to be calculated; this allows the costs of delivering and implementing MENTUPP to be compared with the different measures collected in the outcome evaluation. Multiple incremental cost-effectiveness ratios comparing costs with different outcome measures can then be determined.

Three perspectives will be used in the economic evaluation: an employer perspective, a healthcare perspective and a societal perspective. The employer perspective considers the costs of mental health issues that are borne by the employer in terms of productivity loss as indicated from data from the surveys. The costs of implementing the intervention will be calculated from the surveys, the monitoring instrument, and the log data from the MENTUPP Hub users. The healthcare perspective only includes costs that are expended on healthcare services funded by the health system and will be analysed based on usage of data from the surveys. The societal perspective includes all costs borne by the whole of society, including productivity costs or other costs not borne by the health system or the employer. This will include data from the surveys, the log data from the MENTUPP Hub, and the monitoring instrument to consider time investment and routine rather than research-related travel costs associated with implementing MENTUPP.

Data on the resources required to develop and implement MENTUPP are being collected and appropriate unit costs will be attached to time and materials used. Bespoke questionnaires have been designed to collect data from individual participants in the two arms of the trial on health service use at baseline, 6-month and 9-month follow-up periods; this will be compared with outcome data collected for these individuals over the same time periods. Data on changes in workplace productivity, including absenteeism and presenteeism are also being collected. Country-specific unit costs for healthcare service use, as well as country and industry-specific hourly wage rates, will be applied to all service utilisation and productivity impacts. To allow for multi-country comparison, final costs across countries will be converted into purchasing power parity adjusted international dollars for a common price year using the Campbell-Cochrane Economics Methods Groups EPPI-Centre Cost Converter [80].

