Differences in mean costs will be compared between the two arms of the trial using bias corrected and accelerated bootstrapping. Incremental cost-effectiveness ratios (ICERs) per change in each of the six main outcomes will be calculated at 6-month and 9-month follow-up points. Statistical uncertainty will be explored through bootstrapping 5000 randomly resampled pairs of costs and each of the six outcomes and cost-effectiveness planes will then be drawn.

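### As written, the cost comparison has no country, sector or SME term although prices are country- and industry-specific, so chance differences in participant mix add variance to the arm difference in cost

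*Protocol article*

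**What the plan says.** All references are to the protocol article.

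- **Prices** (Data analysis, Economic evaluation): healthcare use is valued at country-specific unit costs, and "country and industry-specific hourly wage rates, will be applied to all service utilisation and productivity impacts". Totals are then converted to PPP international dollars at one price year.
- **Comparison** (same section): "Differences in mean costs will be compared between the two arms of the trial using bias corrected and accelerated bootstrapping". ICERs are examined with 5,000 bootstrap resamples of cost-outcome pairs. No country, sector or SME term is named, and no resampling unit beyond the pair.
- **Allocation** (Randomisation of SMEs): "group allocation will be conducted in pairs of SMEs within each sector in each country". An unpaired SME is expected to be placed by minimisation on variables that are not listed.
- **Size** (Organisations; Sample size): "SMEs are defined as organisations with fewer than 250 employees". The 65 participants per SME at baseline is an average, and 65% attrition is expected.
- **Contrast** (Data analysis, Outcome evaluation): the six survey measures get mixed-effects models and a between-country analysis. Nothing equivalent is stated for costs.

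**The concern.** Pairing fixes the number of SMEs per arm in each country and sector. It does not fix how many participants each SME contributes. If the larger SME of a pair in a high-wage country falls in one arm, that arm's mean cost rises although nobody there lost more hours. PPP conversion removes general price-level differences but leaves differences in real wages between countries and industries.

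Productivity costs enter the employer and societal perspectives, and the cost difference is the numerator of every ICER. Part of that numerator would reflect where the larger SMEs happen to sit. The mix varies at SME level, so resampling individual pairs, which is the natural reading of the text, does not reproduce its full variability. The trial already allocates within country and sector, so most of this variance can be removed.

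**Working it through.** **The plan's own figure.** The article states: "A sample size of 621 participants (i.e. 27 SMEs with 23 participants) in each arm of the cRCT achieves 85% power". Its other inputs, from the same section, are a target of 0.25 SD, an ICC of 0.05 and two-sided alpha 0.05.

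- Design effect: 1 + (23 - 1) x 0.05 = 2.10.
- Effective size: 621 / 2.10 = 295.7 per arm.
- Power: 0.860 (normal) or 0.847 (t, 52 df). The stated 85% is reproduced. The article gives no corresponding figure for costs.

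**The mechanism.** Take identical resource use and two countries with wages 4 and 1.

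- Arm A, 30 + 16 participants: (30 x 4 + 16 x 1) / 46 = 2.96.
- Arm B, 16 + 30 participants: (16 x 4 + 30 x 1) / 46 = 2.04.
- With 23 + 23 in both arms, both means are 2.50.

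**Size of the wage-mix effect.** From the documents: 9 countries x 3 sectors = 27 cells, one SME per arm per cell (the stated minimum), mean 23 completers. Assumed, because the documents do not give them: wages evenly spaced over nine countries, no sector difference in wages, and the CV of completers per SME.

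SD of the spurious difference, as a share of mean cost, is approximately sqrt(2/27) x size CV x wage CV.

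- Wages 10-30: SD 6.45, mean 20, wage CV 0.323. At size CV 0.6: 0.272 x 0.6 x 0.323 = 5.3% (simulated: 5.2%). The chance of exceeding 5% of mean cost is P(|Z| > 5/5.3), about 34%.
- Simulated SD for size CV 0.4 to 0.8: 2.3-4.6% for wages 15-30, 3.5-6.9% for 10-30, 4.2-8.3% for 8-32.
- A second simulation with geometrically spaced wages, at size CV 0.6, gave SDs of 3.6%, 7.1% and 10.4% for highest-to-lowest wage ratios of 2, 4 and 8. Its mean was about zero (0.06% of mean cost at ratio 4).
- The effect is exactly zero if paired SMEs supply equal numbers, if wages do not differ, or if arms are compared within country and sector.

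**What resampling individuals captures.** For wages 10-30, the individual-level standard error from wage variation is sqrt(2/621) x 0.323 = 1.8%, against the 5.3% above. In the second simulation at ratio 4 and size CV 0.6 it is 2.5% against 7.1%.

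**The comparator: variation in resource use itself.** Take resource-use CV as 1, 2 or 3 (assumed), and borrow the 2.10 design effect for costs (also assumed). The clustered standard error is about sqrt(2/621) x CV x sqrt(2.10) = 8.2%, 16.4% and 24.7% of mean cost. Adding the 5.2% in quadrature:

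- CV 1: sqrt(8.2² + 5.2²) = 9.7%, an increase of about 18%.
- CV 2: 17.3%, an increase of about 5%.
- CV 3: 25.2%, an increase of about 2%.

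A simulation at wage ratio 4 and size CV 0.6, with no SME-level clustering of resource use, gave:

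| Resource-use CV | False-positive rate, individual-level SE | SD, unstratified | SD, within country and sector |
|---|---|---|---|
| 0.5 | 33% | 7.8% | 3.4% |
| 1 | 17% | 9.4% | 6.7% |
| 2 | 9% | 14.7% | 13.8% |
| 3 | 7% | 20.3% | 20.7% |

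The gain from stratifying is clear for moderate variation and disappears when resource use is very skewed.

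**The case against.** The strongest reply is that the article never says the arm means are raw, pooled or unadjusted. BCa bootstrapping describes how uncertainty is obtained and works equally well for an adjusted difference. Covariates and the resampling unit are commonly left to an analysis plan, and that plan is not shown. This stands: no decision against adjustment can be read into the text. What remains is that the article does fix an estimand, an interval method and a resampling scheme for costs. Taken as written, those carry no stratum or SME term.

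The second reply is that this is noise and not bias, and small noise if absence and visits are strongly skewed. This also stands, and the table above shows it. More SMEs than the minimum of 54 would shrink the effect further. Industry wage differences and healthcare prices were not simulated.

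Third, part of the remedy is already planned. Table 1 lists absenteeism, presenteeism and healthcare use separately, and a cost-consequence analysis is specified. Local pricing also suits an employer perspective. Both points are fair, so a common price set is an optional extra and not a correction.

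A reader might infer systematic bias, because employees are recruited after their SME learns its allocation. If, in one arm only, recruitment or retention ran from 20% lower in the lowest-wage country to 20% higher in the highest-wage one, the expected difference would be 2.9%, 5.8% or 8.6% of mean cost at wage ratios 2, 4 and 8. The documents show only that such a pattern is possible. Nothing in them indicates that it will occur.

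**Conclusion.** The point holds as a matter of precision and interval validity. Prices differ by country and industry, participant numbers are not balanced within those strata, and the stated cost comparison has no country, sector or SME term. Chance mix can then separate the arm means when resource use is identical.

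The size is an SD of about 2-8% of mean productivity cost. It rests on assumed wage ranges of 15-30 to 8-32, an assumed size CV of 0.4 to 0.8, and one SME per arm per cell. Set against ordinary variation, for wages 10-30 and size CV 0.6, it adds roughly 2-18% to a clustered standard error as resource-use CV falls from 3 to 1.

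It would be wrong to conclude that arm costs will differ or that the cost comparison is biased. Expectation over randomisations is near zero, and the effect vanishes when paired SMEs contribute equal numbers. It is worth correcting because the remedy uses the factors already used in allocation and costs little.

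**What to change.** In Data analysis, Economic evaluation, state that the cost difference is estimated with adjustment for country and sector, or with both arms standardised to a common country-sector mix. Put the effect in each ICER on the same basis. Additive country and sector terms remove the wage-mix component fully only if wages are additive in the two. Standardising over cells removes it without that condition.

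State also that the bootstrap resamples SMEs within arm, carrying each participant's cost-outcome pair along, and keeps the strata where numbers allow. At the minimum design, a country-by-sector cell holds one SME per arm and cannot be resampled. A country holds three per arm and a sector nine, so the level at which strata are kept should be named.

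Optionally, add a sensitivity analysis that prices all participants from one common set.

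The cost is a few sentences and minor extra analysis work. Country and sector are already needed for allocation, so no new data are required. If resource use proves very skewed, the gain in precision may be nil, but SME-level resampling remains appropriate.

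### The economic bootstrap is described with no SME-level resampling; read as written, it does not fit a trial randomised by SME and would understate uncertainty, most clearly on the effect axis

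*Protocol article*

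**What the plan says.** The protocol article, Data analysis, Economic evaluation, makes two statements about uncertainty. For costs: "Differences in mean costs will be compared between the two arms of the trial using bias corrected and accelerated bootstrapping". For the planes: "Statistical uncertainty will be explored through bootstrapping 5000 randomly resampled pairs of costs and each of the six outcomes". The same section says that health service use is collected by questionnaire from individual participants and set against the outcomes of those same people. The description of the resampling mentions no SME, cluster, stratum or multilevel step.

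Elsewhere the article treats the SME as the unit of the design. Under Randomisation of SMEs, "group allocation will be conducted in pairs of SMEs within each sector in each country". Under Sample size, power is computed for the case "when the intra-cluster correlation is 0.05". Under Data analysis, Outcome evaluation, the survey measures go into mixed models, although the random effects are not listed.

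**The concern.** A bootstrap reproduces the variation of the units it draws. If participants are drawn one by one, the resampled arm means vary as if all participants were independent, and the variation between SMEs is largely lost. In a trial that allocates SMEs, that variation is part of the error of the arm difference. The article fixes the interval type, the figure 5000 and the object resampled, but gives no step that would bring the SME variation in. BCa does not help: it adjusts an interval for bias and skewness, not for a missing variance component.

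At stake are the intervals for mean cost differences, the uncertainty around the ICERs and the spread of points on each plane. The same outcomes could be reported with one precision in the outcome analysis and a tighter one on the plane. Clustering of costs is also plausible. Implementation costs come partly from a monitoring instrument kept per SME, which records research officers' time and travel among other items, and any cost shared across an SME's participants is common to all of them.

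**Working it through.** **Inputs (protocol article, Sample size).** Clusters: "yielding a total of at least 54 participating SMEs, half for intervention and half for control", so 27 per arm. Cluster size: "An average of 65 participants per SME will be recruited at baseline"; "Allowing for an estimated attrition rate of 65" per cent, "this will yield baseline and follow-up data for 23 participants per SME". Check: 65 × 0.35 = 22.75, rounded to 23, and 27 × 23 = 621 per arm. ICC 0.05, difference 0.25 SD, two-sided alpha 0.05, stated power 85%.

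**Step 1: reproduce the stated power.**
- Design effect: DE = 1 + (23 − 1) × 0.05 = 2.10.
- Effective n per arm: 621 / 2.10 = 295.7.
- Standardised difference: 0.25 / √(2 / 295.7) = 3.04. Power = Φ(3.04 − 1.96) = 86.0%.
- A noncentral t gives 84.7% with 52 degrees of freedom and 85.9% with 1240.

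The 85% is reproduced. The protocol's own power therefore rests on a variance inflation of 2.10.

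**Step 2: effect axis under a participant-level bootstrap.** The standard error is too small by a factor of √DE, and a nominal 95% interval covers 2Φ(1.96/√DE) − 1. With DE = 2.10, √DE = 1.449. Intervals have 1/1.449 = 69% of the correct width, and coverage is 2Φ(1.353) − 1 = 82.4%, so 17.6% of intervals miss instead of 5%. This uses equal SME sizes and gives no credit for pairing, as the protocol's own calculation does.

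**Step 3: check by simulation.** Normal data, 27 SMEs of 23 per arm, 1000 simulated trials, 500 percentile-bootstrap replicates each:

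| ICC | Coverage, participants resampled | Coverage, whole SMEs resampled |
|---|---|---|
| 0.01 | 92.5% | 94.1% |
| 0.05 | 83.0% | 93.9% |
| 0.10 | 72.7% | 93.9% |

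**Step 4: costs.** The article gives no cost ICC, so every row below is an assumption (23 per SME, no credit for pairing):

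| Assumed cost ICC | DE | Width relative to correct | Coverage |
|---|---|---|---|
| 0.01 | 1.22 | 91% | 92.4% |
| 0.02 | 1.44 | 83% | 89.8% |
| 0.05 | 2.10 | 69% | 82.4% |
| 0.10 | 3.20 | 56% | 72.7% |

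**Step 5: what pairing can offset.** Let s, c and e be the shares of variance between sector-by-country strata, between SMEs within a stratum, and between individuals, with s + c + e = 1. In a balanced paired design the stratum part cancels from the arm difference, while a plain participant bootstrap still counts it as noise. The ratio of true to bootstrap variance is (23c + e)/(s + c + e).
- s = 0: the ratio is 1 + 22c, the design effect above.
- The ratio is 1 when s = 22c. For example c = 0.01, s = 0.22, e = 0.77 gives 0.23 + 0.77 = 1.00, so no understatement.
- c = 0.05, s = 0.22, e = 0.73 gives 1.15 + 0.73 = 1.88, so standard errors are still too small by √1.88 = 1.37.

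**Step 6: cells available for resampling.** Nine countries × three sectors = 27 cells. With 54 SMEs that is two per cell, one per arm.

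**The case against.** The strongest reply is that the article never says participants are resampled. The figure 5000 exceeds the 2 × 621 = 1242 analysed participants, so it most likely counts replicates. Keeping costs and outcomes in pairs is equally a feature of a cluster or two-stage bootstrap. A condensed article may leave the resampling unit to the full analysis plan, and clustering is recognised elsewhere. This stands in part: a reader might infer that the plan states outright that it draws individuals and disregards SMEs, and the text does not go that far. What remains is a specific method, applied to person-level data, with no step that fits the design. Followed as written, it is a participant-level bootstrap.

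The second reply concerns size, and it stands. A reader might carry the 82% coverage over to the cost intervals, or suppose that costs cluster at least as strongly as outcomes because wages and unit costs differ by country and industry. The documents support neither. The ICC of 0.05 belongs to change in outcome. Country and sector cost levels are largely balanced by the paired allocation, and Step 5 shows that this can offset some or even all of the understatement for costs. Pairing does not remove cost variation specific to an SME.

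Third, the article states no cost hypothesis, willingness-to-pay threshold or decision rule, and the primary effectiveness analysis is untouched. That stands too and limits the severity.

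**Conclusion.** The concern holds as a mismatch between the bootstrap as described and a trial randomised by SME. It does not establish that the investigators will resample participants. On the effect axis the size follows from the protocol's own figures: a standard error too small by a factor of about 1.45 and coverage of about 82%, given participant-level resampling, 23 analysed participants in every SME, and the ICC of 0.05 taken wholly as variation between SMEs that pairing does not remove. For costs the direction is probable but not fixed, and the size is an assumption: coverage of about 92% to 82% over ICCs of 0.01 to 0.05, before any offset from pairing. Severity is moderate: it affects the precision claimed for the economic results, not the main test of effectiveness.

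**What to change.** State the resampling unit and make it the SME. Any of these would do:

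- Resample whole SMEs with replacement within arm, stratified at most by sector. This counts country differences as noise, so it may be somewhat too wide.
- Resample the sector-by-country SME pairs, which follows the allocation. The plan must then say how any SME allocated without a partner enters.
- Fit a bivariate mixed model for cost and outcome with SME random effects and sector and country effects.

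In both bootstraps, keep each participant's cost and outcome together and use 5000 replicates. If BCa is kept, its acceleration term should be computed by leaving out SMEs or pairs, not participants. Do not resample SMEs within arm inside sector-by-country cells: at the planned minimum a cell holds one SME per arm, so every draw returns the same SME and no between-SME variance is restored. Use one method for mean cost differences, ICERs and planes.

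The cost is analysis code only, with no change to data collection. Intervals will generally be wider. If the full analysis plan already specifies such a method, a single clarifying phrase settles the point.
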